##### Individual course evaluation

2.2.2.1

Individual courses within the educational program are evaluated using a brief participant satisfaction survey. This survey comprises six items addressing various dimensions of the courses, including its informational content, practical relevance, motivational impact, perceived level of difficulty, effect on participants’ competence, and organizational quality. Respondents indicate their level of agreement with each statement on a five-point Likert scale ranging from “strongly agree” to “strongly disagree.” In addition to these closed-ended items, participants are invited to elaborate on their ratings and to provide suggestions or requests for future courses through open-ended questions. This approach allows for both quantitative and qualitative insights into participants’ perceptions and experiences. This formative evaluation enables timely responses to participants’ feedback and supports iterative conceptual refinements for subsequent cohorts. Participation in this component of the evaluation is determined on a course-by-course basis.

##### Self-perception on professional knowledge and competence on CIH

2.2.2.2

To contextualize the competence improvement assessment following each individual course, at T0, T1 and T2 the self-perception of professional knowledge and competence in CIH will be investigated using a single-item measure. Participants will be asked, “How would you rate your current professional knowledge and competence in integrative oncology?” Responses were indicated on a slider scale ranging from 0 (“very low”) to 100 (“very high”).

##### German version of the University of the West of England Interprofessional Questionnaire

2.2.2.3

This questionnaire was developed for the longitudinal evaluation of interprofessional curricula and comprises four scales assessing key interprofessional dimensions which will all be assessed at T0, T1 and T2. The Communication and Teamwork scale captures participants’ experiences with communication and teamwork in group settings. This scale does not include a neutral response option, based on the assumption that all respondents have prior experience in this domain. The Interprofessional Learning scale assesses participants’ attitudes toward interprofessional learning as well as perceptions of the timing of educational interventions. The Interprofessional Interaction scale addresses perceptions of the quality of interprofessional interactions in healthcare work environments. Both the Interprofessional Learning and Interprofessional Interaction scales consist of nine items each. The fourth scale, Interprofessional Relations, comprises eight items and evaluates relational aspects of interprofessional collaboration. With the exception of the Communication and Teamwork scale, all items are rated on a five-point Likert scale ranging from 1 (strongly agree) to 5 (strongly disagree). Scale scores reflect participants’ attitudes toward the assessed domains and differentiate between positive, neutral, and negative orientations (31). The validity, reliability, and psychometric properties of the German translation were examined in a study conducted in 2016, demonstrating good psychometric quality, with internal consistency coefficients ranging from 0.75 to 0.90 and a well-fitting underlying factor structure (32). The UWE-IP was selected because it captures key dimensions of interprofessional learning and collaboration that are directly addressed in the counseling and communication components of the INSIGHT learning objectives (see Supplementary File 1).

##### German version of the interprofessional socialization and valuing scale 9a/b

2.2.2.4

This questionnaire focuses on socialization processes within the work environment, with particular emphasis on healthcare teams and will be collected during T0, T1 and T2. Following the initial publication of a 21-item version, a psychometrically equivalent 9-item version with pre- and post-test specifications was validated in English (33). The German version of the original 21-item scale was validated in 2022 and demonstrated high internal consistency (Cronbach’s *α* = 0.90) (34). To contribute to the ongoing validation efforts at the University Hospitals of Heidelberg and Tübingen, the ISVS-9a/b will be applied in the present study. The ISVS-9a/b was chosen because it reflects the program’s aim of fostering interprofessional socialization in the context of integrative oncology counseling and directly corresponds to the interprofessional collaboration learning objectives.

##### German version of the extended professional identity scale

2.2.2.5

This scale operationalizes Extended Professional Identity Theory, which builds on concepts derived from social identity theory and identity theory. It comprises three subscales assessing interprofessional belonging, interprofessional commitment, and interprofessional beliefs (35). The German version demonstrates good internal consistency (Cronbach’s *α* = 0.89) and consists of 12 items distributed across the three aforementioned subscales (36). The EPIS-G will be collected at T0, T1, and T2. The EPIS-G was included to capture changes in professional identity (belonging, commitment and beliefs), which may be influenced by participants repeated engagement in interprofessional learning activities, including longitudinal work on case examples and exposure to perspectives from different healthcare professions. In line with these learning activities, we aim to explore whether participation in the program is associated with changes in participants professional identity with regard to interprofessional collaboration.

#### Data analysis

2.2.3

Sociodemographic variables, individual course evaluation and self-perception on professional knowledge and competence on CIH will be analyzed descriptively. Scores obtained from the applied instruments (UWE-IP, ISVS 9A/9B, and EPIS-G) will be compared across the three measurement time points within the same sample. Primary analyses will be descriptive and will include measures of central tendency (means, medians), measures of dispersion, and graphical visualization of temporal trends.

The distributional properties of the data will be examined using the Shapiro–Wilk test in conjunction with visual inspection of Q–Q plots. Exploratory within-subject comparisons across time points (T0, T1, and T2) will be conducted to assess potential changes in scores over time. For normally distributed data, repeated-measures analysis of variance (ANOVA) will be applied, whereas the Friedman test will be used for non-normally distributed data. Given the limited sample size, all inferential analyses will be interpreted in an exploratory manner. Where notable differences are observed, *post hoc* analyses (e.g., pairwise Wilcoxon signed-rank tests with Bonferroni correction) may be performed to further describe changes between specific time points.

Attrition between T0, T1, and follow-up (T2) will be reported using flow diagrams and descriptive statistics (e.g., number and proportion of participants at each time point, reasons for drop-out where available). For within-subject analyses of change over time, only participants with data at the relevant time points will be included. Comparisons of key baseline characteristics between completers and non-completers will be considered to explore potential attrition bias. Missing data will be handled using a complete case approach for analyses of within-subject change over time. No imputation across time points or at the participant level is planned, given the exploratory design and limited sample size. At the item level, person-mean imputation within a scale will be considered if missing responses do not exceed a predefined threshold and the extent and patterns of missing data will be reported descriptively.

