#### Study design and data collection

2.2.2

The evaluation study is designed as a longitudinal, prospective, single-arm, non-controlled, non-randomized observational pre–post study with follow-up. Given the limited sample size resulting from the restricted enrollment of the educational program, an exploratory analytical approach is adopted. Data will be collected at three time points per cohort: baseline (T0) on the introductory day of the program, at program completion (T1), and at a 6-month follow-up after completion (T2).

At T0, during the first event of the educational program, sociodemographic data will be collected using a standardized questionnaire to characterize the study population. Collected variables include age (categorized), gender, and stratified professional experience. Healthcare profession and professional role within the workplace (e.g., junior or senior physician) will also be assessed. Data collection will be conducted using the online platform SoSci Survey (version 3.8.00) and during the individual courses as well as T0, T1, and T2 a specific timeframe is reserved for the participation in the questionnaires. To support complete data entry, reminder prompts for unanswered items are integrated into the online questionnaire platform.

As an interprofessional educational program focusing on interprofessional counseling in integrative oncology, the primary objective of the evaluation is to examine interprofessional parameters as well as changes in self-perception on professional knowledge and competence on CIH, as detailed below. Given that the curriculum is interprofessional in both its mode of delivery and its intended application, questionnaires addressing interprofessional dimensions constitute the fundamental component of the evaluation approach.

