The planned prospective pre-post evaluation using validated interprofessional instruments allows an initial assessment of changes in self-perceived competencies and attitudes. However, the non-controlled design limits causal inference, and reliance on self-report measures may introduce social desirability bias or response-shift effects. Long-term follow-up is also needed to determine whether educational gains translate into sustained practice change and improved interprofessional collaboration. Performance-based assessments or observational examinations, such as objective structured clinical examinations, may offer a more objective evaluation option increasing the validity of the findings. However, after intensive discussion within the research team, the decision was made not to implement such assessments due to the substantial resources required for their administration and execution. Participants travel from across Germany, so on-site time is deliberately kept to a minimum to support compatibility with work and everyday life, with a clear focus on the acquisition of practical skills. Therefore, participant-reported assessments were chosen for the evaluation of the educational program. While the curriculum is explicitly designed for direct transfer into professional practice and to equip participants with competencies for interprofessional CIH counseling, the present evaluation focuses on self-reported competence and interprofessional outcomes and does not include performance-based assessments of counseling in real-world clinical encounters, which limits the extent to which actual practice change can be investigated.

If positively evaluated, the INSIGHT curriculum could serve as a scalable model for integrating evidence-based CIH education into oncology training programs and cancer center structures. Such initiatives may contribute to safer integrative care, improved communication about CIH use, and more informed shared decision-making, which are increasingly recognized as essential components of high-quality oncology care.

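### Change in self-rated CIH competence is named in the primary objective, but the analysis section leaves the item out of the within-subject comparison and specifies no paired change summary for it

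*Protocol article*

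**What the plan says.** The objective is in section 2.2.2 (Study design and data collection): "the primary objective of the evaluation is to examine interprofessional parameters as well as changes in self-perception on professional knowledge and competence on CIH". The second component is worded as a change. The same section adds that "questionnaires addressing interprofessional dimensions constitute the fundamental component of the evaluation approach", so the two components do not carry equal weight.

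Section 2.2.2.2 gives the measurement: "at T0, T1 and T2 the self-perception of professional knowledge and competence in CIH will be investigated using a single-item measure". The response is a slider from 0 to 100.

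Section 2.2.3 (Data analysis) opens with the analysis of this item: "Sociodemographic variables, individual course evaluation and self-perception on professional knowledge and competence on CIH will be analyzed descriptively". The next sentence deals with the questionnaires: "Scores obtained from the applied instruments (UWE-IP, ISVS 9A/9B, and EPIS-G) will be compared across the three measurement time points within the same sample". The slider is not on that list. The section continues: "Primary analyses will be descriptive and will include measures of central tendency (means, medians), measures of dispersion, and graphical visualization of temporal trends". It then describes exploratory within-subject comparisons of scores by repeated-measures ANOVA or the Friedman test. The complete-case rule, and the restriction to people with data at the time points concerned, are stated for analyses of within-subject change.

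The Discussion (section 4) says that the evaluation "allows an initial assessment of changes in self-perceived competencies and attitudes".

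**The concern.** The objective asks whether self-rated competence changes, and the data are collected to answer that. The analysis section places the item with the sociodemographic variables and the course satisfaction survey, and keeps the same-sample comparison for the other three instruments. It gives no reason for treating the two components of one objective differently. This is a stated assignment, so an unseen analysis plan that followed the article would carry the mismatch forward.

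Two things are at stake. First, summaries produced separately at T0, T1 and T2 do not show how individuals moved, and their SDs do not give the precision of the mean change. Second, the rule that keeps the same people in a comparison is tied to within-subject analyses, and this item is not clearly one of them. If fewer people answer at T1 or T2, its means may describe different groups. Section 2.2.3 itself recognises the possibility of attrition bias.

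The item matters because the three questionnaires measure interprofessional attitudes, socialization and identity. The slider is the only measure repeated at T0, T1 and T2 that asks about competence in integrative oncology itself.

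**Working it through.** **The plan's own figure.** Section 2.2.1 gives three cohorts of at most 25 participants: 3 × 25 = 75, which agrees with the stated maximum. The article gives no SD, correlation, drop-out rate or effect size, so the rest is illustration on assumed inputs.

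**Step 1: the two components side by side.**

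| | Interprofessional questionnaires | Self-rating slider |
|---|---|---|
| Named in primary objective | yes | yes, as a change |
| Measured at T0, T1, T2 | yes | yes |
| Descriptive analysis | yes | yes |
| Listed for same-sample comparison over time | yes | no |
| Exploratory ANOVA or Friedman | yes | not on the natural reading |
| Complete-case rule for change | yes | not clearly |

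The word scores in the paragraph on within-subject comparisons could be stretched to include the slider. It most naturally refers back to the three instruments just named.

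**Step 2: what pairing is worth.** Assume n = 75 at both time points, an SD of 20 points at each, and a within-person correlation ρ of 0.3 to 0.7. The 95% half-width for the mean change is:

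- paired: t(0.975, n − 1) × SD × √(2(1 − ρ)) / √n
- from separate summaries: t(0.975, 2n − 2) × SD × √(2/n)

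| ρ | Paired | Separate summaries | Ratio |
|---|---|---|---|
| 0.3 | 5.4 | 6.5 | 1.2 |
| 0.5 | 4.6 | 6.5 | 1.4 |
| 0.7 | 3.6 | 6.5 | 1.8 |

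Over an SD of 15 to 25, the paired half-width runs from 2.7 to 6.8 points and the other from 4.8 to 8.1.

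**Step 3: what drop-out can do.** Let d be the share of participants missing later, and g the baseline mean of those who stay minus that of those who leave. The T0 mean of everyone is the stayers' T0 mean minus d × g. The later mean of the stayers minus the T0 mean of everyone is therefore the stayers' true change plus d × g.

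- d = 0.2, g = 5: shift 1 point
- d = 0.2, g = 10: shift 2 points
- d = 0.4, g = 5: shift 2 points
- d = 0.4, g = 10: shift 4 points

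If those who leave start higher, the shift has the opposite sign. Nothing in the article supports a particular size or direction.

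**The case against.** The strongest defence is that the plan is exploratory throughout. The primary analyses are descriptive for every outcome, and the ANOVA and Friedman tests are exploratory for the questionnaires too. All the slider lacks is an exploratory comparison. Describing a single item without testing it is defensible in a single-arm study of at most 75 people. Section 2.2.2.2 also gives the item a contextual role beside the course-by-course competence ratings. All of this stands, and it limits the severity. It does not explain why the same exploratory comparison is given to the other instruments and withheld from an item in the same objective.

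A reader might infer that the plan cannot estimate the change at all. The documents do not support that. The item is measured three times, section 3 refers to individual pseudonyms, and a difference between two time-point means is a point estimate. Among the same respondents it equals the mean within-person change. Nor does the article say that the item will be summarised only time point by time point: a descriptive analysis can include change scores, and trend plots are planned.

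A reader might also take the slider to be half of the primary objective, or the only competence measure. The article calls the interprofessional questionnaires fundamental, and the course survey includes a rating of the effect on competence, though that rating has no baseline.

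The lack of a stated confidence interval is not particular to this item. None is named for the questionnaires, and such detail may sit in a fuller document. Attrition is also partly covered: flow diagrams, numbers at each time point and reasons for drop-out are planned, and a comparison of completers with non-completers will be considered.

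**Conclusion.** The point holds as a mismatch between objective and analysis. A change named in the primary objective is assigned to descriptive reporting and left off the list of same-sample comparisons. No paired change summary is specified for it, and the complete-case rule for change does not clearly reach it. A mean difference would still be available, but read from separate summaries it lacks the precision that pairing gives and can absorb differences between those who stay and those who leave.

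On the assumed inputs, an interval built from separate summaries is about 1.2 to 1.8 times as wide as the paired one. Drop-out of 20% to 40% with a baseline gap of 5 to 10 points would move the apparent change by 1 to 4 points. These figures show the mechanism and do not predict this study's result.

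Severity is moderate. No confirmatory test, sample size or formal decision depends on the item, and the Discussion already acknowledges the limits of an uncontrolled, self-reported evaluation.

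**What to change.** In section 2.2.3, take the slider out of the sentence that groups it with the sociodemographic variables and add it to the exploratory within-subject comparison. Report the mean (or median) within-person change from T0 to T1 and from T0 to T2 with 95% confidence intervals, among participants observed at both time points concerned. Show the T0 summary twice: for all participants, and for those also observed later. The second display lets the reader see any effect of drop-out directly.

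The cost is one sentence and one more exploratory analysis. It needs no new data, item or visit. Because the first cohort began in October 2025, the change should be dated and made before the follow-up responses are examined.

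### Change in self-rated CIH competence is one of two named parts of the primary objective, but the analysis section leaves it out of the within-person comparison over time

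*Protocol article*

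**What the plan says.** Three places in the protocol article give this item a role.

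- **Section 2.2.2 (Study design and data collection):** "the primary objective of the evaluation is to examine interprofessional parameters as well as changes in self-perception on professional knowledge and competence on CIH". The same paragraph adds that "questionnaires addressing interprofessional dimensions constitute the fundamental component of the evaluation approach".
- **Section 2.2.2.2 (Self-perception):** "at T0, T1 and T2 the self-perception of professional knowledge and competence in CIH will be investigated using a single-item measure", answered on a slider from 0 to 100. The stated purpose is "To contextualize the competence improvement assessment following each individual course".
- **Section 2.2.3 (Data analysis):** in one sentence with the sociodemographic data and the course ratings, "self-perception on professional knowledge and competence on CIH will be analyzed descriptively". The next sentence reads "Scores obtained from the applied instruments (UWE-IP, ISVS 9A/9B, and EPIS-G) will be compared across the three measurement time points within the same sample".

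Section 2.2.3 goes on to make the primary analyses descriptive (central tendency, dispersion, plots of trends). It adds exploratory within-subject comparisons by repeated-measures ANOVA or the Friedman test, with optional pairwise follow-up tests. Within-subject analyses of change use only participants with data at the relevant time points. No confidence interval is mentioned for any outcome.

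**The concern.** The objective asks for change in the self-rating, and the data to measure change within each person will exist. Yet the sentence naming the scores to be compared within the same sample omits it, and the sentence that does name it groups it with background variables. The same item is therefore a primary-objective measure in one section, context in another and a descriptive variable in a third.

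This matters because the slider is the only measure of CIH knowledge and competence taken at all three time points. The other three instruments cover interprofessional attitudes, socialisation and identity, and the course surveys are tied to single courses. The Discussion nevertheless says that the design permits a first look at change in self-perceived competence.

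Two things are at stake. The same-participants rule is written for within-subject analyses, so an item outside them may be summarised on a different set of people at each wave. And means and standard deviations per wave do not give the precision of a paired change, because they carry no information on the within-person correlation.

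**Working it through.** **1. The sections side by side**

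| Element | Self-rating (0–100) | UWE-IP, ISVS-9a/b, EPIS-G |
|---|---|---|
| In the primary objective (2.2.2) | Yes, as change | Yes, as interprofessional parameters |
| Collected at T0, T1, T2 | Yes (2.2.2.2) | Yes (2.2.2.3 to 2.2.2.5) |
| Descriptive analysis (2.2.3) | Yes | Yes |
| Listed for comparison across time in the same sample (2.2.3) | No | Yes |

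The two parts of the objective differ only in the last row. The later sentence on exploratory within-subject comparisons speaks of scores, the word just used for the three listed instruments.

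**2. The plan's own figure**

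Section 2.2.1 gives a maximum sample of 75. Three cohorts of at most 25 give 3 × 25 = 75, so it reproduces. The article states no standard deviation, within-person correlation or dropout rate. Everything in steps 3 and 4 is therefore illustration under assumed values.

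**3. Precision of the change**

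Assume equal standard deviation SD at both waves, n pairs and within-person correlation r.

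- Paired standard error = SD × √(2(1 − r)/n)
- Standard error if the waves are treated as independent = SD × √(2/n)
- Ratio, unpaired to paired = 1/√(1 − r)

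The ratio depends on neither SD nor n:

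- r = 0.3: 1/√0.7 = 1.20
- r = 0.5: 1/√0.5 = 1.41
- r = 0.7: 1/√0.3 = 1.83

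95% half-widths for a mean change, in SD units, using t quantiles (n − 1 degrees of freedom paired, 2n − 2 unpaired):

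| n | Paired, r = 0.3 | Paired, r = 0.5 | Paired, r = 0.7 | Unpaired |
|---|---|---|---|---|
| 75 | 0.272 | 0.230 | 0.178 | 0.323 |
| 60 | 0.306 | 0.258 | 0.200 | 0.362 |
| 45 | 0.355 | 0.300 | 0.233 | 0.419 |

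**4. Mixing participants across waves**

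Assume that 15 of 75 drop out after T0, that their baseline ratings averaged 10 points below those of completers, and that nobody's rating changes. The T0 mean of all 75 lies 10 × 15/75 = 2 points below the T0 mean of the 60 completers. The T1 mean comes from completers only, so the wave summaries show a 2-point gain that no one experienced. A paired change in the 60 completers shows zero.

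**The case against.** The case for leaving the plan alone has real substance.

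- **Primary analyses are descriptive for every scale.** This stands. The self-rating lacks only the exploratory comparison that the other scales receive. A reader might infer that a primary analysis is missing; the text does not support that.
- **The two parts of the objective are not equal.** This also stands. Section 2.2.2 calls the interprofessional questionnaires fundamental, section 2.2.2.2 presents the item as context, and the abstract names only the three scales besides sociodemographics. A reader might say that half of the primary objective goes unanswered; the article gives no such weighting, and a descriptive answer is planned.
- **A descriptive analysis may include change scores, and the word scores might cover the slider.** This stands in part. The article does not rule out a paired summary, so one cannot say that the report will contain no change estimate. But the listing in section 2.2.3 points the other way, and for a measure in the primary objective the text should not be left open.
- **No confidence intervals are planned for any outcome.** True. The self-rating is not singled out in that respect, and the interval proposed below is an addition.
- **The precision ratio is a general identity under assumed correlations.** True. It shows what separate wave summaries leave out; it does not show that this study would reach a wrong conclusion.
- **An interval does not cure self-report bias.** True. The Discussion already acknowledges social desirability and response shift.

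None of these points reconciles an objective stated as change with an analysis list that leaves that change out.

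**Conclusion.** The mismatch is real and modest. One of the two named parts of the primary objective is change in a rating measured at all three time points, and the analysis section leaves that rating out of the within-person comparison and hence out of its same-participants rule. What is missing is exploratory, in a study that describes itself as exploratory.

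The inconsistency rests on the text alone. Its size rests on assumptions: for a within-person correlation of 0.3 to 0.7 and equal variances, an unpaired standard error is about 1.2 to 1.8 times the paired one. The dropout artefact is 2 points on the 0 to 100 scale in the single scenario shown, and scales with the share lost and with how far their baseline differs from that of completers.

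**What to change.** In section 2.2.3, take the 0 to 100 self-rating out of the sentence that makes it purely descriptive and add it to the scores compared across T0, T1 and T2. Report the paired change from T0 to T1 and from T0 to T2 among participants with both values, each with a 95% confidence interval and labelled exploratory. Ideally give the three scales in the same form, so that the single item is not reported more fully than the validated instruments. Reword section 2.2.2.2 so that the item's role matches the objective in section 2.2.2.

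If the sponsor intends the item only as context, the alternative is to remove it from the primary objective in section 2.2.2. Either route settles the inconsistency.

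The cost is a sentence or two and one more variable in a within-subject analysis already planned. The confidence intervals are a small addition, computed from the same data. No new data, participant burden or sample is needed. Recruitment runs through the 2027/2028 cohort, so the wording can be settled before the data set is complete.

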#### Recruitment and sample size

2.2.1

Participants for the evaluation study will be recruited from three consecutive INSIGHT cohorts (2025/2026, 2026/2027, and 2027/2028) Participation in the educational program is independent of participation in the evaluation study. As enrollment in INSIGHT is limited to 25 participants per cohort a maximum sample size of 75 participants can be achieved and no sample size calculation was conducted. Inclusion criteria for the evaluation study include a minimum age of 18 years, fluent command of the German language, and enrollment in INSIGHT. The study’s objectives and relevant information will be provided during the initial lecture of the program, which will take place during the online launch event. During this event, informed consent will be obtained and T0 data collection conducted.

Admission criteria for INSIGHT comprise completion of an academic degree in a health profession or a completed vocational training in a health profession with a minimum of 2 years of professional experience. In addition, a professional connection to oncology is required.

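### Bonferroni for the three pairwise time contrasts is valid but needlessly conservative; Holm gives the same family-wise control and never rejects less

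*Protocol article*

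**What the plan says.** Section 2.2.3 of the protocol article plans the following for the UWE-IP, ISVS-9 and EPIS-G scores: "Exploratory within-subject comparisons across time points (T0, T1, and T2) will be conducted to assess potential changes in scores over time". The omnibus step depends on the distribution: for normal data "repeated-measures analysis of variance (ANOVA) will be applied, whereas the Friedman test will be used for non-normally distributed data". Pairwise tests come next, under the condition "Where notable differences are observed". They are optional, and the method is given as an example: "pairwise Wilcoxon signed-rank tests with Bonferroni correction". The condition has no p-value threshold, and the section names no alpha.

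Two further statements set the context. The same section says that "all inferential analyses will be interpreted in an exploratory manner". Section 2.2.1 says that "a maximum sample size of 75 participants can be achieved and no sample size calculation was conducted".

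**The concern.** There are exactly three time points, so there are three contrasts per scale: T0–T1, T0–T2 and T1–T2. Bonferroni holds each of them to one third of alpha, however small the other p-values are. Step-down methods relax that threshold once a contrast has been rejected and still keep the family-wise error at alpha. The number of participants cannot be raised above the enrolment cap, and within-subject analyses use complete cases only. Power lost to an avoidable choice of correction can therefore be recovered only in the analysis. T0–T1 and T0–T2 are the contrasts that answer the pre-post and follow-up questions. T0–T2 gains more in power points from a better correction.

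**Working it through.** **The plan's own figure.** 25 participants × 3 cohorts = 75, as section 2.2.1 states. No alpha, power or effect size is given to reproduce.

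**Thresholds, with an assumed two-sided alpha of 5%.**
- Bonferroni: every contrast at 0.05/3 = 0.0167.
- Holm: smallest p-value at 0.05/3 = 0.0167; if rejected, the next at 0.05/2 = 0.025; if rejected, the last at 0.05/1 = 0.05.

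Holm's thresholds are never below Bonferroni's, so Holm rejects whatever Bonferroni rejects. The two part where the smallest p-value is at or below 0.0167 and the second lies between 0.0167 and 0.025, or where the first two are rejected and the third lies between 0.0167 and 0.05. Holm keeps strong family-wise control at 5% under any dependence between the tests.

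**Size of the gain.** Simulation, 20,000 replicates per row. All of the following are assumptions: normal scores with SD 1; correlations 0.6 (T0–T1), 0.5 (T0–T2) and 0.7 (T1–T2); Wilcoxon signed-rank contrasts with no omnibus gate; n = 45, 60 or 75, because attrition is not quantified. Gains from T0 are in SD at T1/T2. Cells show power in %, Bonferroni → Holm.

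| n | Gains | T0–T1 | T0–T2 |
|---|---|---|---|
| 45 | 0.3/0.3 | 39.1 → 41.2 (+2.1) | 30.6 → 33.6 (+3.0) |
| 45 | 0.3/0.2 | 39.3 → 40.3 (+1.0) | 12.7 → 15.5 (+2.8) |
| 60 | 0.3/0.3 | 53.3 → 55.5 (+2.2) | 42.2 → 46.2 (+4.0) |
| 60 | 0.3/0.2 | 53.0 → 53.9 (+0.9) | 17.6 → 21.8 (+4.2) |
| 75 | 0.3/0.3 | 64.7 → 67.0 (+2.3) | 53.0 → 57.2 (+4.2) |
| 75 | 0.3/0.2 | 65.1 → 66.1 (+1.0) | 23.0 → 27.9 (+4.9) |

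The Monte Carlo standard error of one cell is at most √(0.5 × 0.5/20,000) = 0.35 points.

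**Family-wise error in the same runs.**
- All three time points equal: 4.0–4.1% for Bonferroni and the same for Holm, because the first step is identical.
- T1 = T2 with T0 different: 1.6–1.7% for Bonferroni, 2.5–3.2% for Holm.
- Three unadjusted 5% tests without a gate, all time points equal: 11.7–12.2% (if independent, 1 − 0.95³ = 14.3%). Some protection is therefore needed.

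**The alternative with a formal gate.** With three means on one common sample, any two pairwise equalities imply the third. Every combination of two or more pairwise nulls is then the global null. By closed testing, an omnibus rejection at 5% lets each contrast be tested at 5% with family-wise error still at 5%. With a Friedman gate, the same runs gave 3.8–4.0% (all equal) and 3.4–4.2% (T1 = T2). Gate plus Bonferroni gave 2.3–2.4% and 1.3–1.5%.

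Compared with Bonferroni without a gate, the Friedman-gated closed test is a trade-off. At n = 75 with gains 0.3/0.2, T0–T2 rises from 23.0% to 32.6% but T0–T1 falls from 65.1% to 56.4%. A separate 10,000-replicate run gave 22% to 32% and 64% to 56%. At n = 75 with gains 0.3/0.3, T0–T2 is 57.1% against Holm's 57.2%, and T0–T1 is 61.1% against Holm's 67.0%.

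An ANOVA gate must also hold its own level. Under strong non-sphericity (correlations 0.2/0.2/0.9), the uncorrected test rejected in 7.0–7.5% of null trials, and the closed test's family-wise error reached 5.6–6.5%.

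**The case against.** The strongest reply is that little depends on this. The primary analyses are descriptive, all inference is exploratory, the pairwise tests are optional, and Bonferroni is only an example. No family-wise claim is made, Bonferroni is a valid method, and an analysis plan could settle the choice. All of that stands, and it is why the point is minor. It does not remove the point: Bonferroni is the only multiplicity method the article names, so it is the likely default, and Holm is no worse in any data set.

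A reader might go further and infer that Bonferroni pays twice for protection the omnibus test already gives, so that each contrast could simply be tested at 5%. The article does not support this. Its gate is "Where notable differences are observed", with no threshold and no alpha. Under an informal gate, Bonferroni is the only stated protection and cannot simply be dropped. The larger gains that this reading suggests, such as 45% to 60% for T0–T2 at n = 60 with gains of 0.3 SD, compare against Bonferroni behind a strict 5% gate. They also use a Greenhouse-Geisser-corrected ANOVA and paired t-tests. The article names neither that correction nor paired t-tests.

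Two technical limits also stand against the closed test. The article says that "only participants with data at the relevant time points will be included", so contrasts could rest on different subsets; two pairwise nulls then imply the third only if dropout is unrelated to change. And the Wilcoxon null concerns symmetry of the paired difference about zero, so two such nulls do not strictly imply the third. Holm needs neither condition.

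**Conclusion.** The point holds as a minor efficiency improvement. Bonferroni in section 2.2.3 controls the error it is meant to control, and it would be wrong to call it an error. It is nevertheless dominated by Holm, which needs no gate and has the same family-wise guarantee. That Holm never rejects less is a mathematical fact and rests on no assumption. The size of the gain does rest on assumptions: about 3–5 power points for T0–T2 and about 1–3 for T0–T1, given alpha 5%, normal scores, effects of 0.2–0.3 SD, correlations 0.6/0.5/0.7 and 45–75 complete cases. Unadjusted 5% contrasts are not justified by the plan as written. Even with a proper Friedman gate, they can cost power on the pre-post contrast. The conclusion covers the three contrasts within one scale score and says nothing about multiplicity across the several scales.

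**What to change.** In section 2.2.3, or in the analysis plan if there is one, name Holm instead of Bonferroni as the correction for the T0–T1, T0–T2 and T1–T2 contrasts within each scale score. The gate wording need not change for this.

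If the team prefers the closed test, with each contrast at 5%, it should state three things in advance: that contrasts are tested only when the omnibus p-value is at or below 0.05; that a sphericity correction is used with the repeated-measures ANOVA; and that all contrasts use the same complete cases as the omnibus test.

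The Holm option costs one word and standard software. It needs no extra data and loses no error control.
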